**Hypotheses:**

**1)** Biweekly β-D-glucan surveillance will identify SICU patients with an invasive fungal infection (IFI) before clinical signs or symptoms develop.

1. Anidulafungin initiated in response to a positive β-D-glucan test (i.e. preemptive therapy) will be well tolerated, safe, and effectively treat patients early, before advanced infection is established.
2. Peripheral blood gene expression signatures obtained serially from at-risk patients can predict early IC.

**Study Design:** Single center, randomized, non-blinded, parallel group, comparative study.

**Sample Size:** 100 subjects; 75 in the active surveillance/preemptive therapy arm and 25 in the usual care arm.

**Study Population:** Adult patients admitted to Duke University Medical Center SICU at-risk for the development of IC.

**Study Drug:** Intravenous anidulafungin initiated in response to a positive β-D-glucan test for subjects in the active surveillance/preemtpive arm. Preemptive treatment will continue for at least 14 days or until ICU discharge (maximum 28 days), which ever is longer.

**Efficacy:** IFI assessments will be made weekly and at SICU discharge.

**Safety:** A data safety monitoring board will review adverse events every 4 months.

**Statistics:** β-D-glucan test characteristics will be described using sensitivity, specificity, positive and negative predictive values. The proportions of patients developing proven or probable IC in each group will be compared using Fisher’s exact test. The prevalence of treatment emergent adverse events will be described using summary statistics. For gene expression analysis, we will designate subjects diagnosed with a *Candida* bloodstream infection as case patients and those who remained uninfected and had negative B-D-glucan testing as controls. Decision tree analysis will be used to develop predictive signatures for candidemia versus no infection.

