**Preemptive Antifungal Therapy Based on Fungal Biomarkers**

β-D-glucan (BDG) is a cell wall constituent found in many pathogenic fungi including *Aspergillus* and *Candida* as well as *Fusarium*, *Trichosporon*, *Saccharomyces,* and *Acremonium*. Assays that are capable of detecting BDG in the serum of patients with IFI due to these organisms have been developed commercially. The β-D-glucan test (Fungitell^™^; Associates of Cape Cod, Falmouth, MA) is FDA approved as an adjunct to the diagnosis of deep-seated mycoses and fungemia. BDG analysis performed on serial serum samples obtained from 283 patients with acute myeloid leukemia or myelodysplastic syndrome who were receiving antifungal prophylaxis revealed that the test became positive a median of 10 days before the clinical diagnosis of IFI in 100% of patients(13). Absence of a positive test result had a 100% negative predictive value and a single positive test result had a specificity of 90%.

Primary prevention strategies that incorporate serial measurement of fungal biomarkers with initiation of antifungal therapy in response to a positive test represent an exciting new approach to IC management. Early initiation of appropriate antifungal therapy has been shown to improve clinical outcomes, but to date, the BDG assay has only been validated for patients with hematological malignancies and/or following transplantation. The performance of the test in the ICU setting has not been established. Poor specimen handling, hemodialysis using certain cellulose membranes, exposure to gauze products, some antibiotics, and recent receipt of albumin or immunoglobulin products may cause false positive test results in some patients(14-18). Since many of these potential sources of BDG cross-reactivity are present in the ICU population (**Table 2**), further investigation of the assay is warranted in this setting.

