**Active surveillance/ preemptive therapy group**

Subjects in this arm of the study will have serum drawn twice a week for BDG testing while in the SICU, with the results of the test reported to the managing clinicians in real-time. Subjects will receive intravenous (IV) anidulafungin should the β-D-glucan exceed 60 pg/ml on a single determination. A positive test cut-off of 60 pg/ml was selected based on the observation that 81% of patients with IC will have a positive test at this level(25). Preemptive therapy will continue for a minimum of 14 days or for as long as the subject remains in the ICU up to a maximum of 28 days duration.

If the BDG test turns positive and preemptive therapy is initiated, serum will then be collected every other day to assess the kinetics of the BDG test on anidulafungin treatment. Kinetic monitoring will continue until the test becomes negative at which time twice weekly assessments will be resumed and continue for as long as the patient remains in the SICU. Samples collected while patients are receiving anidulafungin will be batched and run retrospectively. Clinicians will not have these results made available for use in real-time. However, once preemptive anidulafungin therapy is completed and the drug has been stopped, biweekly monitoring with results reported to the medical team will be resumed. Subjects, however will not be restarted on anidulafungin should the test again turn positive after a course of preemptive therapy is completed.

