**STATISTICAL METHODOLOGY**

**Sample Size**

Targeted enrollment is 100 adult SICU patients. This study will not be powered to show a difference in the efficacy of preemptive management versus standard care due to single center population constraints in addition to cost limitations. Sample size calculations were therefore based on the number of adult patients expected to be admitted to the SICU over a 1 year period who are likely to meet inclusion criteria (n=700). Based on prior experience, it is reasonable to expect an accrual of 100 patients in a year. Using a 3:1 randomization strategy, 75 will be assigned to active surveillance and 25 to standard care. We estimate that 25% of patients will develop a positive test(13;25;27) and 19 will receive anidulafungin. These numbers should provide sufficient data for a preliminary feasibility evaluation of the preemptive strategy.

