**Statistical Analyses**

Statistical analysis will be performed using SAS software. P values and 95% confidence intervals will be 2-tailed and statistical significance set at the 5% level unless otherwise specified.

*Demographics and Baseline Characteristics*

Demographic and baseline characteristic information will be summarized and compared using the Chi-squared test for discrete variables and one way ANOVA for continuous various to assess any imbalance between treatment groups.

*β-D-glucan Test Characteristics*

β-D-glucan test characteristics, using data collected from standard care group, will be described using sensitivity, specificity, positive and negative predictive values. Proven and probable cases of IFI, as defined by EORTC/MSG criteria (**tables 3 and 4**), will constitute the standard for comparison.

*Feasibility Analysis*

Feasibility will be a description of preemptive protocol adherence, BDG test requests off schedule, and the number of patients withdrawn from the preemptive arm due to the initiation of empiric systemic antifungal therapy in the absence of a positive BDG test.

*Efficacy End-Points*

Development of IFI during the study period will be assessed by the principal investigator (PI) and a second blinded investigator using predefined EORTC/MSG criteria for proven or probable disease. The study period is defined as the time the patient was cared for in the SICU. The proportions of patients developing IFI, and IC specifically, in each group will be compared using Fisher’s exact test. The median ICU stay and number of febrile days while in the ICU will be compared using the Kruskal-Wallis test. Patient mortality, overall and attributed to IFI, will also be summarized by group. Response-to-therapy (RTT) will be determined by the PI and a blinded second investigator. The RTT population will consist of all patients who were underwent BDG monitoring for at least 3 days and received at least 1 dose of systemic antifungal therapy.

*RNA Analyses*

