**Data Analysis**

Data Analysis will be performed after completion of data entry, database closure, and verification of database accuracy. All primary and secondary analyses will be performed on the intent-to-treat basis.

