**Table 5. Clinical Response**

| **Clinical response*** | **Definition** |
| --- | --- |
| Response to empiric therapy | Resolution of fever and/or other attributable symptoms/signs of IFI |
| Response to preemptive therapy | Resolution of abnormal BDG test result |

*Clinical response as an efficacy endpoint will be assessed at the end of treatment.

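### Response to preemptive therapy needs no infection and can be met by BDG clearance alone, so a false-positive test that clears without any drug effect counts as an efficacy success

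*Protocol*

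**What the plan says.** Under Efficacy End-Points (Statistical Analyses), the response-to-therapy set is all patients who "underwent BDG monitoring for at least 3 days and received at least 1 dose of systemic antifungal therapy". Proven or probable infection is not a condition of entry. In the preemptive arm anidulafungin is given "should the β-D-glucan exceed 60 pg/ml on a single determination", with no confirmatory test.

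Preemptive response is defined twice. Table 5 asks only for "Resolution of abnormal BDG test result", and its footnote treats clinical response as an efficacy endpoint judged at the end of treatment. The Clinical Response paragraph under End Point Definitions asks for a normal BDG and, if fever or signs were present when the test turned positive, for those to resolve as well. Empiric response in the standard-care arm does not use BDG under either definition.

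The introduction lists causes of false-positive results and says that "many of these potential sources of BDG cross-reactivity are present in the ICU population". Table 2 tabulates them and the schedule for all subjects records them weekly, but neither response definition uses them. The standard-care section states that BDG accuracy in SICU patients is unknown.

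**The concern.** One of the stated hypotheses is that preemptive anidulafungin will "effectively treat patients early, before advanced infection is established". Response to therapy is the endpoint closest in wording to that claim. As defined, it takes credit for any BDG that returns to negative, whatever the cause. If the positive result came from albumin, gauze, a dialysis membrane or an antibiotic, and the exposure ended, the test could clear with or without the drug. Other things equal, more self-clearing false positives give a higher response rate, so a less specific test would make the drug look better. The standard-care response rate cannot expose this, because it measures something else. A reader given a single response percentage could not separate treatment of early infection from the natural course of a false-positive assay.

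**Working it through.** **Inputs from the protocol**
- Arm sizes (Sample Size): "75 will be assigned to active surveillance and 25 to standard care".
- Positivity and number treated (Sample Size): "We estimate that 25% of patients will develop a positive test(13;25;27) and 19 will receive anidulafungin".
- Sensitivity for IC at the 60 pg/ml cut-off: 81% (Active surveillance/preemptive therapy group).
- Specificity of a single positive: 90%, from a leukaemia/myelodysplasia cohort, not the SICU (Preemptive Antifungal Therapy Based on Fungal Biomarkers).

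**Assumptions, because the protocol gives no figure**
- IC risk p: 5%, 10% and 20%. The 10% in the epidemiology section is a level at which experts favour prophylaxis, not a forecast for this trial.
- Clearance c: the share of false-positive tests that are negative by end of treatment without a drug effect, 50% to 100%.
- Infected patients are set to zero response.

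**Step 1. The plan's own figure.** 75 × 0.25 = 18.75, rounded to 19. It reproduces. The same rate in standard care gives 25 × 0.25 = 6.25, about 6 positives.

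**Step 2. Uninfected share of those treated.** U = 1 − 0.81 × p / 0.25.

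**Step 3. Response with no drug effect under Table 5.** R = U × c. R passes 50% when c > 0.5 / U.

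| IC risk p | U | R at c = 50% | R at c = 75% | R at c = 100% | c needed for R > 50% |
|---|---|---|---|---|---|
| 5% | 84% | 42% | 63% | 84% | 60% |
| 10% | 68% | 34% | 51% | 68% | 74% |
| 20% | 35% | 18% | 26% | 35% | not reachable |

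U exceeds one half only if p < 0.5 × 0.25 / 0.81 = 15.4%.

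**Step 4. The stricter text definition.** Assume for illustration that half of these patients are febrile when the test turns positive, that fever resolves in half of them, and c = 90%. The multiplier is 0.90 × (0.5 + 0.5 × 0.5) = 0.675. R is then 0.676 × 0.675 = 46% at p = 10% and 0.838 × 0.675 = 57% at p = 5%, against 61% and 75% under Table 5 at the same clearance.

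**Step 5. Can the protocol's figures settle p?** Applied once per patient, 81% sensitivity, 90% specificity and 25% positivity imply p = (0.25 − 0.10) / (0.81 − 0.10) = 21%, with 0.81 × 0.211 / 0.25 = 68% of positives infected. Surveillance is repeated, however. Two independent tests at 90% specificity each give 0.81 × 0.10 + (1 − 0.90²) × 0.90 = 25.2% positive at p = 10%, of whom 0.171 / 0.252 = 68% are uninfected. Both readings fit 25% positivity, so the figures do not settle it.

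**The case against.** The strongest objection is that the size is assumed. A reader might infer that the protocol expects most treated patients to be uninfected, or that it calls false positives common and transient. It says neither: it says that the listed factors may cause false positives in some patients and that potential sources are present in the ICU. It gives no clearance rate, and dialysis, albumin or antibiotics may continue through treatment. A reader might also infer that response will exceed 50% with no drug effect. That needs both a low IC risk and high clearance, and the text definition lowers the figure. These objections stand, and the point does not rest on either stronger reading.

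A second objection is that no between-arm test of response is planned. The objective is to evaluate response, while neighbouring objectives say compare. This also stands. It weakens the inference that the response set breaches the statement "All primary and secondary analyses will be performed on the intent-to-treat basis": response can be scored only in treated patients, so a treated subset is a weak conflict. The different triggers for treatment in the two arms matter only if the two rates are set against each other.

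Third, the endpoint is one of twelve secondary endpoints in a study not powered for efficacy, and IFI incidence, breakthrough IFI and mortality address the treatment hypothesis without BDG. This limits the importance but does not remove the defect. An unseen analysis plan could add stratified reporting, but the protocol itself fixes the population and the success criterion and calls the result an efficacy endpoint.

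**Conclusion.** The point holds in this form: the population requires no infection, Table 5 accepts BDG clearance alone, and nothing in the plan measures clearance without preemptive therapy against the same criterion. That follows from the text without any assumption.

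The size is undetermined. At an assumed 10% IC risk, no-effect response under Table 5 ranges from 34% to 68% for clearance of 50% to 100%. Across the three risks examined the range is 18% to 84%. Even at 20% risk, about a third of treated patients would be uninfected and could be scored as successes. The documents do not support a claim that the rate must exceed 50% or that most treated patients will be uninfected. This is a moderate defect in the interpretation of a secondary, unpowered endpoint and should be corrected.

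**What to change.** In Efficacy End-Points and Table 5:

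1. Reconcile Table 5 with the Clinical Response paragraph so that preemptive response has one definition.
2. Report response separately for treated patients with and without proven or probable IFI, distinguishing IFI present at initiation from breakthrough IFI, and by exposure to the Table 2 factors. Scoring infected patients only would be cleaner but leaves about 6 of 19 at 10% risk (19 × 0.324), drops the patients treated before infection is documented, and includes breakthrough cases selected on failure. Showing both groups is the better choice.
3. Label BDG clearance in all treated patients as test kinetics, not efficacy.
4. Add a descriptive comparison, by randomised arm, of patients whose first BDG at or above the cut-off comes from a scheduled post-randomisation draw (about 19 versus 6). Exclude off-schedule tests, which only the preemptive arm may have. Report later proven or probable IFI, and BDG status at a common time point available in both arms; sampling turns to every other day in the preemptive arm after a positive, so the time point must be stated.
5. Describe the standard-care result as clearance under usual care, not untreated clearance, because those patients may receive antifungals at any time. Show their antifungal use beside it.

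The cost is analysis wording: the samples, IFI assessments and exposure records are already planned. The drawback is small sets, so the results can only be descriptive.

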**INTRODUCTION**

**Epidemiology of Invasive Candidiasis**

Fungal infections are devastating to human health and have lethal consequences for both immunocompromised and critically ill patients in the Intensive Care Unit. *Candida* species are now the 4^th^ most common cause of bloodstream infection in the United States (1), with the vast majority of these infections being nosocomially acquired(2). Most *Candida* blood stream infections (BSIs) are due to *C. albicans* followed in frequency by *C. glabrata*, a species that is generally less susceptible to traditional antifungal therapy (i.e., fluconazole). Despite the availability of newer antifungal drugs, the mortality attributable to invasive candidiasis (IC) remains extremely high (3). One reason that IC is so devastating is the difficulty in establishing a timely diagnosis. The clinical presentation of IC is highly variable and nonspecific, and standard blood culture is notoriously insensitive. In addition to the clinical impact, IC is a burden on the healthcare system, with estimates of increased costs on the order of $40,000 US dollars per episode(4;5).

Patients in the ICU have a higher incidence of *Candida* BSI as compared to those on general medical/surgical wards(1). Given that IC carries such a high associated morbidity, mortality, and cost, prophylactic antifungal therapy has been proposed as a way to prevent disease in high-risk patient populations. Azoles and polyenes have both been studied as prophylaxis in the ICU setting and were shown to decrease the incidence IFIs without impacting overall mortality(6-10). Individual prophylaxis studies, however, have varied widely with regard to patient selection and antifungal regimen. No consensus on the optimal preventative strategy currently exists, but experts have advocated some form of antifungal prophylaxis in situations where the rate of IC is expected to approach 10%(11).

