Initial signature development cohort: RNA from patients with blood cultures growing *Candida* and an equal number of patients with negative blood cultures and negative BDG testing (controls) will be chosen for signature development. A decision tree approach used previously by our group will be used to find gene expression patterns that are correlated with candidemia to determine the predictive capability of those gene patterns as a diagnostic test(28;29). Once we identify a large number (100-300) of gene expression patterns that significantly correlate with the illness classification in our initial cohort, we will then identify the best combination of 3-5 patterns for discriminating between those with candidemia and those with no infection. Once the best expression patterns are identified, we will perform cross validation analysis in which we construct a decision tree with the best gene patterns using all of the samples except for one “held out” sample. We can then use the decision tree model to predict the classification of the “held out” sample as an honest test of the accuracy of our predictive model and to guard against over-fitting. We plan to define host gene expression patterns in response to candidemia using an initial cohort of up to 30 persons with candidemia and up to 30 persons with no infection. This sample size has 90% power to detect at least a 2-fold change in expression levels in the 70% least variable genes with an alpha of 0.001(30). After establishing robust gene expression signatures that classify individuals as having a “candidemia” or “no infection” we will test the generalizability of these profiles on the remaining patients presenting to the intensive care unit at risk for invasive candidiasis. We will not know beforehand the etiology of their symptoms.

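### The equal-number rule for signature controls leaves most of the 30 permitted control places empty when candidemia cases are few, and the 90% power statement holds only with 30 cases

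*Protocol*

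**What the plan says.** Protocol, Statistical Methodology, RNA Analyses: the development cohort consists of candidemia cases, identified by blood culture, plus controls, for whom the rule is: "an equal number of patients with negative blood cultures and negative BDG testing (controls) will be chosen for signature development". The same section then describes "an initial cohort of up to 30 persons with candidemia and up to 30 persons with no infection" and makes this claim for it: "This sample size has 90% power to detect at least a 2-fold change in expression levels". The claim is limited to the 70% of genes that vary least and uses alpha 0.001. Patients outside this cohort are kept for a later test of generalizability.

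Other places that bear on this:
- Sample Size: enrolment is 100, and 25% are expected to become BDG-positive.
- All Subjects: an RNA tube is drawn twice weekly from every patient, and the RNA is analysed retrospectively.
- Chart of Study Procedures (footnote h) and RNA Analysis Methods: both describe the controls without an equal-number limit.
- Epidemiology of Invasive Candidiasis: the only rate given is a benchmark, with prophylaxis advocated "in situations where the rate of IC is expected to approach 10" per cent. It is not a forecast for this trial. Under End Point Definitions, invasive candidiasis (IC) also includes proven deep-tissue infection.

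**The concern.** Cases are the scarce group and controls the plentiful one. With 25% expected to be BDG-positive, about 75 of the 100 patients could serve as controls before the culture and antifungal criteria are applied, and their RNA is already in store. Tying the number of controls to the number of cases gives up precision that the written ceiling of 30 controls would allow. The rule binds whenever there are fewer than 30 cases, which is nearly certain at plausible rates. The 90% power statement is attached to the full 30 v 30 cohort, so a reader may take it to describe what this trial will deliver.

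**Working it through.** **Inputs from the protocol.** Ceiling of 30 cases and 30 controls; 90% power; 2-fold change (1.0 on the log2 scale); alpha 0.001; 100 patients. The general rule is "P values and 95% confidence intervals will be 2-tailed", so alpha is taken as two-sided. The array calculation does not restate this.

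**Assumptions.** 5 to 10 candidemia cases per 100 patients; normal data on the log2 scale.

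**1. The stated 90%.** It cannot be reproduced independently because no standard deviation is given. It can be solved for. For m cases and c controls, pooled t-test power = P(T > t_crit), with T noncentral t, df = m + c − 2 and noncentrality d × √(mc/(m + c)). At 30 v 30, df = 58, t_crit = 3.466 and √15 = 3.873. Power is 90% at d = 1.239 (noncentrality 4.80), an SD of 1/1.239 = 0.807. This describes a gene at the limit of the 70% least variable.

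**2. Does the rule bind?** Thirty cases in 100 patients need a 30% rate. The binomial probability of 30 or more is about 2 × 10⁻⁸ at a 10% rate and 0.01 at 20%. With 5 to 10 cases, 30 − 10 = 20 to 30 − 5 = 25 control places stay empty.

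**3. Per-gene power at d = 1.239, pooled t.**

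| Cases | 1:1 noncentrality / t_crit | Power at 1:1 | 30 controls noncentrality / t_crit | Power with 30 controls |
|---|---|---|---|---|
| 5 | 1.96 / 5.04 | 2.9% | 2.56 / 3.61 | 17.6% |
| 8 | 2.48 / 4.14 | 10.4% | 3.11 / 3.58 | 34.1% |
| 10 | 2.77 / 3.92 | 17.9% | 3.39 / 3.57 | 44.5% |

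Part of the gain is a smaller standard error and part is the lower critical value from more degrees of freedom. The normal approximation ignores the second part (SD re-solved as 0.847). It gives 7.7%, 17.6% and 25.8% at 1:1 against 19.9%, 37.3% and 47.7%.

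**4. Without pooling the variances.** Welch's test, simulated at the same d with equal SDs, gives about 2%, 9% and 16% at 1:1 against 10%, 22% and 33% with 30 controls.

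**5. If cases vary more.** I assumed a case SD 1.5 times the control SD and kept the difference at 1.239 control SDs (400,000 simulated data sets per setting). Welch power for 5, 8 and 10 cases goes from about 1%, 4% and 7% at 1:1 to 3%, 6% and 10% with 30 controls. The pooled test's false-positive rate with 30 controls is about 1.1%, 0.8% and 0.6% instead of 0.1%, while at 1:1 it stays near 0.1%. Welch's is about 0.4%, 0.2% and 0.15% with 30 controls, so with 5 cases it is not fully protected either.

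**6. Less variable genes.** With 10 cases and pooled t, an SD of 0.5 gives 69.5% at 1:1 and 96.3% with 30 controls; an SD of 0.4 gives 92.5% and 99.9%.

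**7. Can controls restore 90%?** The equivalent number per group is 2mc/(m + c). For 10 v 30 this is 600/40 = 15. It can never exceed 2m, which is 20 for 10 cases, against the 30 per group behind the stated power.

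**The case against.** The strongest defence is that balance is a reasonable choice. A 1:1 comparison is robust to unequal variances, and step 5 shows that both the gain and the error rate depend on them. That stands, and it is why the fix names the test. It does not justify the rule outright, since more controls raised power under both tests in every setting above.

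The unselected controls are also not wasted: patients outside the cohort serve the generalizability test. With 10 cases, going from 10 to 30 controls reduces the remainder from 100 − 20 = 80 to 100 − 40 = 60 patients. This is a real cost, though 60 is still a usable set.

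Three stronger readings are tempting, and the protocol supports none of them:
- **An array budget of 60, mostly unspent.** The text gives two ceilings on persons and no array count or budget. Since early and late candidemia signatures are both sought (Secondary Endpoints), one case may need several arrays. Filling to 60 with 50 to 55 controls would break the ceiling of 30 and take most of the roughly 75 BDG-negative patients.
- **Power is one third of what it could be.** Against filling to 60, that ratio appears with 10 cases by pooled t (17.9% v 54.7%). Over 2 to 10 cases and both calculation methods it runs from 0.04 to 0.47, and it is 0.70 at an SD of 0.5 with 10 cases.
- **The 1:1 mix falsifies the predictive values.** The protocol promises predictive values for the BDG test, not for the signature. For the signature it promises held-out classification and then a test in the remaining patients. Any PPV contrast needs a sensitivity and specificity that the protocol does not give, and balancing class weights would bring back the same effective 50% prevalence.

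**Conclusion.** The point holds in a limited form. The equal-number rule works against the protocol's own allowance of 30 controls. With 5 to 10 cases, using that allowance raises per-gene power at the variability limit from about 3–18% to 18–45% by pooled t, or from 2–16% to 10–33% by Welch. These figures rest on an assumed case count, a back-solved SD and, for the main comparison, equal variances. The gain shrinks if cases are more variable than controls.

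A reader might infer that a better ratio would rescue the stated 90%. It would not: the binding limit is the number of cases, and step 7 shows that no number of controls makes up for it. Nor do these figures measure how well a tree built on 3 to 5 patterns classifies patients. The signature is a secondary objective, though also a study aim in the synopsis, and no treatment or visit is affected. The change is worthwhile but modest.

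**What to change.** In RNA Analyses:
1. Replace the equal-number wording with: all eligible controls, up to the stated maximum of 30.
2. Compare genes with a test that does not assume equal variances: Welch, or a permutation test, preferably of the Welch statistic. With 5 v 5 a permutation test has only 252 arrangements (10 choose 5), so its smallest two-sided p-value is 2/252 = 0.008 and it cannot reach 0.001. With 5 v 30 there are 324,632 arrangements.
3. State that the 90% holds only with 30 cases and 30 controls, and give power for the realistic range of cases with the SD used.
4. If a PPV or NPV is reported for the signature, base it on the candidemia rate observed in the trial, not on the sampled case-to-control ratio.

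**Cost.** The control rule is one sentence; the power sentence must change as well. Extra arrays are run within the ceiling already written, and no new recruitment or blood draw is needed. Fewer control-type patients remain for the generalizability test (about 60 of 100 patients in all with 10 cases and 30 controls), and the tree is trained on an unbalanced set.

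### Gene patterns are chosen on all development samples before leave-one-out, so the cross-validated accuracy is biased upward and is not the honest test the protocol claims

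*Protocol*

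**What the plan says.** The protocol, Statistical Methodology, RNA Analyses, gives the steps in a fixed order.

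1. Controls are matched in number to the candidemia cases: "an equal number of patients with negative blood cultures and negative BDG testing (controls) will be chosen for signature development". The cohort is capped at "up to 30 persons with candidemia and up to 30 persons with no infection".
2. A label-driven screen comes first: "Once we identify a large number (100-300) of gene expression patterns that significantly correlate with the illness classification in our initial cohort".
3. A second label-driven choice follows: "we will then identify the best combination of 3-5 patterns for discriminating between those with candidemia and those with no infection".
4. Cross-validation starts when both choices are finished: "Once the best expression patterns are identified, we will perform cross validation analysis".
5. Within a fold, the step described is the tree: "we construct a decision tree with the best gene patterns using all of the samples except for one" held-out sample.
6. The held-out prediction is then presented "as an honest test of the accuracy of our predictive model and to guard against over-fitting".

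The section goes on to plan a check of the finished profiles on the remaining enrolled patients, whose diagnosis will not be known beforehand. The Synopsis and RNA Analysis Methods also name the decision-tree approach; neither says that selection is repeated in each fold.

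**The concern.** Leave-one-out estimates accuracy without bias from selection only if the omitted sample played no part in building the classifier. Here its class label has already helped decide which patterns passed the screen and which 3-5 were kept. With thousands of candidates and at most 60 samples, some patterns separate the classes by chance. Those are the ones selected, and they still separate the classes when one of the same samples is set aside afterwards.

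Rebuilding the tree does protect against over-fitting of its splits and cut-points. It does not cover the search over the array, which is the larger source of optimism.

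At stake is the accuracy reported for the candidemia signature. This is the last of the secondary endpoints and also one of the three aims in the Synopsis. The Introduction looks ahead to a rapid assay built on such signatures.

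**Working it through.** **Inputs from the protocol.** 100-300 patterns, then 3-5; at most 30 cases and 30 controls; 1:1 controls; leave-one-out with a decision tree; enrollment of 100 (Sample Size).

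**Not in the protocol, so assumed.** The number of genes on the array (10,000-30,000), independent Gaussian expression, tree depth (2 or 3), and the number of candidemia cases.

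**The plan's own figure.** The section states no expected accuracy, only a power: "This sample size has 90% power to detect at least a 2-fold change in expression levels in the 70% least variable genes", at alpha 0.001. A 2-fold change is 1 unit on the log2 scale. With n = 30 per group, power of 90% requires

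SD = sqrt(n/2) / (z_alpha + z_0.90) = sqrt(15) / (3.29 + 1.28) = 0.85 (two-sided, normal).

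The one-sided version gives 3.873 / (3.09 + 1.28) = 0.89, and the two-sided noncentral-t version 0.81. No gene SD is given, so the 90% is plausible but can be neither confirmed nor refuted. The point below does not depend on it.

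**Null simulation.** No gene differs between classes, so true accuracy is 50%.

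- Set-up A: keep the 200 genes with the largest |t| on all samples, choose 3 or 5 of them on all samples, then run leave-one-out refitting only a depth-3 tree.
- Set-up B: 20,000 genes, best 4 by t on all samples, depth-2 tree; run twice.

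Mean leave-one-out accuracy, planned order, single tree:

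| Set-up | 30+30 | 10+10 | 5+5 |
|---|---|---|---|
| A: 5 by forward selection, 10,000 genes | 72% | 84% | 99% |
| A: 5 by forward selection, 30,000 genes | 72% | 86% | 100% |
| A: 3 by forward selection, 10,000 genes | 74% | 85% | 99% |
| A: top 5 by t, 10,000 genes | 71% | 77% | 99% |
| A: best of 300 random 5-subsets by tree fit, 10,000 genes | 76% | 71% | not run |
| B: two runs | 67%, 73% | 81%, 79% | 100%, 100% |

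If patterns are taken as principal components of gene clusters rather than single genes, the averages are 84% at 30+30 and 82% at 10+10.

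**Spread.** Over 150 null data sets (set-up A, 5 by forward selection, 10,000 genes), accuracy reached at least 80% in 17% of them at 30+30, 75% at 10+10 and 100% at 5+5. It reached at least 90% in 1%, 37% and 97%.

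**Selection inside each fold.** Set-up A gives 48% at 30+30 (25 runs) and 44% at 10+10 (60 runs). Set-up B gives 44-55% in one run and 39-43% in the other. Fresh null samples give 50%. Values somewhat below 50% are expected of leave-one-out with balanced classes, because removing a sample puts its own class in the minority. The optimism is gone.

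**Which sample size is likely?** The only rate of invasive candidiasis in the text is the 10% in the Introduction, a threshold for considering prophylaxis and not a forecast for this trial. If it applied to candidemia, the expected count would be 100 × 0.10 = 10, and the binomial probability of 30 or more would be about 2 × 10^-8. Reaching 30 cases on average needs a 30% rate (100 × 0.30 = 30). The protocol's definition of invasive candidiasis also includes deep-tissue infection, so candidemia alone cannot be more frequent.

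**What is left for the later test.** With 10 cases and 10 controls in development, 100 - 20 = 80 patients remain. If all 10 cases were used for development, none of the 80 has candidemia and sensitivity cannot be estimated.

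**The case against.** The strongest reply is that the same section plans a second check on patients outside the development cohort, with diagnosis not known beforehand. That stands as a real safeguard. A reader might infer that the trial would end up announcing a signature built on noise; the documents do not support going that far, because a null signature could fail this test. The Chart of Study Procedures speaks of arrays in selected culture-positive patients, so it is not certain that every case enters development. But the second check does not correct the cross-validated figure, and it can test sensitivity only if cases are left over.

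A reader might also infer that the accuracy will look excellent whatever happens. It need not: at the 30+30 ceiling a single tree on pure noise averages about 67-76%, clearly inflated but not excellent. Near-perfect figures appear at about 5 per group, a count the protocol does not state.

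Nor does the scheme give no protection at all, since refitting the tree guards its own splits. The simulations are a simplified version of the plan: real genes are correlated, which may reduce the inflation. Linear or centroid rules show larger inflation but are not planned, so nothing here rests on them.

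Finally, the signature is a secondary endpoint analyzed retrospectively, for research only. No primary endpoint and no patient's care depends on it.

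**Conclusion.** The point holds. The protocol fixes an order in which both label-driven selections precede the hold-out, and its claim of an honest test is wrong as written. This is not a detail left open for an analysis plan.

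The size depends on the case count. Under a complete null, single-tree accuracy averages about 67-76% at 30+30, 71-86% at 10+10 and 99-100% at 5+5, against a true 50%. These figures assume 10,000-30,000 independent Gaussian genes and a shallow tree. If candidemia occurred in about 10% of patients, which is an assumption, there would be about 10 cases, where the bias is large.

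It should be fixed because the signature is a stated aim. It is not a threat to the feasibility, test-performance or safety endpoints.

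**What to change.** - Repeat the 100-300 screen, the choice of 3-5 patterns and the tree building inside every fold, so that the held-out sample is untouched until it is predicted.
- Add a label-permutation test of the whole pipeline.
- Report the nested estimate as the accuracy, and remove the honest-test wording for the current scheme.
- Lock the signature before applying it to the remaining patients, and report how many of them had candidemia.

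The cost is a change of text, some computing time and a less favorable reported accuracy. No extra patients, samples or arrays are needed, and because the RNA work is done after study completion, conduct of the trial is not affected.
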